## 1.2 PURPOSE AND SCOPE OF THE PLAN

This document details the proposed analysis of the primary objective and some secondary objectives for the study “Benefits of Aldosterone Receptor Antagonism in Chronic Kidney Disease (BARACK D)”.

The statistical analysis plan will be available on request when the principal papers are submitted for publication in a journal. Suggestions for subsequent analyses by journal editors or referees, will be considered carefully, and carried out as far as possible in line with the principles of this analysis strategy; if reported, the source of the suggestion will be acknowledged. The health economic analysis and analysis of the pilot study are not covered here.

It is not intended that the strategy set out in the plan should prohibit sensible practices. However, the procedures established in the plan will be followed as closely as possible when analysing and reporting the trial. Any modifications and the reasons for those will be fully noted.

Any analysis-related decisions may need to be made based on the pilot study data and observed data from the main trial, such as the distribution of the follow-up data. These decisions will be made prior to the proposed statistical analyses. Any post-hoc exploratory analyses completed to support planned analyses which were not stated in this SAP will be documented and reported in the appendices to the clinical study report. Some flexibility in the desire for pre-planning is anticipated because, for example, further analyses will be expected to be undertaken on the basis of the results of planned analyses.

The plan draws on statistical guidance ICH Harmonised Tripartite Guideline: Statistical Principles for Clinical Trials, and PSI Guidelines for Standard Operating Procedures for Good Statistical Practice in Clinical Research, the CONSORT statement for reporting trials and PC-CTU statistical SOPs.

Any deviations from the statistical analysis plan will be described and justified in the final report of the trial.

The analysis to address the objective looking at treatment costs and benefits is outside the scope of this statistical analysis plan. Analysis to address the costs and benefits will be detailed in a separate health economic analysis plan.

### 1.3 TRIAL OVERVIEW

Chronic kidney disease (CKD) is a major cause of increased mortality and morbidity through increased vascular events and progression to end stage renal failure (ESRF) [1]. These increased events result in CKD having high cost to healthcare systems, with the dialysis required in ESRF benchmarked as at the maximum acceptable cost effectiveness threshold for an intervention by most healthcare systems. However, the most important component of CKD in terms of mortality and morbidity is cardiovascular disease (CVD) [2]. There is a graded inverse relationship between cardiovascular risk and estimated glomerular filtration rate (eGFR), independent of age, sex and other risk factors [3-6] or for creatinine [7]. While the cardiovascular risk of end-stage CKD is extreme, in public health terms the burden resides in early stage (CKD stages 1-3) disease, which is more prevalent, affecting around 40% of those over 70 years. When added to conventional risk factors, renal markers substantially improve risk stratification and CKD is therefore an important and under-recognised risk factor for CVD in the general population [8]. Although the risks of myocardial infarction and other manifestations of coronary artery disease are increased in CKD, the pattern of CVD is atypical, with a much greater incidence of heart failure and sudden cardiac death than in the general CVD population [9-11].

Currently, few therapies have proved effective in modifying the increased CVD risk or the rate of renal decline in CKD. There are accumulating data that aldosterone receptor antagonists (ARAs) may offer cardio-protection and delay renal impairment in patients with the CV phenotype in CKD. The use of ARA in CKD has therefore been increasingly advocated and even termed the 'renal aspirin' [12]. To date, however, no large study of ARAs with renal or CVD outcomes is underway.

This trial evaluates the benefits of an ARA, spironolactone, in patients with stage 3b CKD.

## 1.4 OBJECTIVES

|                   | Objectives                                                                                                                                                                          | Outcome Measures                                                                                                                                                                                                                                                                                                                                                                                                                                                                                                                                          | Timepoint(s)                                     |
|-------------------|-------------------------------------------------------------------------------------------------------------------------------------------------------------------------------------|-----------------------------------------------------------------------------------------------------------------------------------------------------------------------------------------------------------------------------------------------------------------------------------------------------------------------------------------------------------------------------------------------------------------------------------------------------------------------------------------------------------------------------------------------------------|--------------------------------------------------|
| Primary           | To determine the effect of aldosterone receptor antagonism on mortality and cardiovascular outcomes (onset or progression of cardiovascular disease) in patients with stage 3b CKD. | 
Time from randomisation until the first occurring of:
 
 
• Death or
 
• Hospitalisation for heart disease (coronary heart disease, arrhythmia, atrial fibrillation, sudden death, resuscitated sudden death), stroke, transient ischaemic attack, peripheral arterial disease or heart failure or
 
• First onset of any condition listed above not present at baseline.
 
 
Primary endpoints will be adjudicated by an independent endpoints committee blinded to treatment arm.
 | Time from randomisation to first occurrence      |
| Primary Long term | To determine the effect of aldosterone receptor antagonism (even short-term use) on long term mortality and cardiovascular outcome in patients with stage 3b CKD.                   | 
Annual rates of:
 
 
• Death,
 
• Hospitalisation for heart disease (coronary heart disease, arrhythmia, atrial fibrillation, sudden death, resuscitated sudden death), stroke, transient ischaemic attack, peripheral arterial disease or heart failure.
 
• First onset of any condition listed above not present at baseline.
 
                                                                                                                                                       | Annual rates, collected via medical notes review |

|           |                                                                                                                                                                            |                                                                                                                                                                                                                                                                                   |                                                                                                                          |
|-----------|----------------------------------------------------------------------------------------------------------------------------------------------------------------------------|-----------------------------------------------------------------------------------------------------------------------------------------------------------------------------------------------------------------------------------------------------------------------------------|--------------------------------------------------------------------------------------------------------------------------|
| Secondary | 
To determine the effect of adding an aldosterone receptor antagonism in patients on 1-5 below:
 
1. The individual components of the composite primary outcome
 | 
 
Hospitalisation or new onset heart disease (coronary heart disease, arrhythmia, atrial fibrillation, suddendeath, resuscitated sudden death), stroke, transient ischaemic attack, peripheral arterial disease or heart failure.
 
 | 
 
Total occurrences
 
                                                      |
|           | 2. Measures of cardiovascular haemodynamics                                                                                                                                | 
 
Change in blood pressure annually and at final visit.
 
                                                                                                                                                                           | 
 
Annually and at final visit.
 
                                           |
|           | 3. Measures of renal function                                                                                                                                              | 
 
Changes in NP
 
Change in ACR
 
Changes in eGFR
 
                                                                                                                                                                   | 
 
Change from baseline, annually and to final visit for NP, ACR and eGFR
 
 |
|           | 4. Healthcare cost evaluation                                                                                                                                              | 
 
Change in health status on EQ-5D-5L, KDQoL, (ICECAP-A and QoL VAS – Oxford only) and NHS resource use (records).
 
                                                                                                                | 
 
Change from baseline, annually and to final visit
 
                      |
|           | 5. Safety                                                                                                                                                                  | 
 
Rates of hypotension (<100mmHg systolic or >20 mmHg systolic drop on standing)
 
Rates of adverse events
 
Rates of hyperkalaemia
 
                                                                           | 
 
Total occurrences
 
Total occurrences
 
                           |

| Secondary Objectives                                                                                                                                                       | Secondary Endpoints                                                                                                                                                                                                                                                                | Timepoint(s) for assessment of this outcome measure (if applicable)                                                      |
|----------------------------------------------------------------------------------------------------------------------------------------------------------------------------|------------------------------------------------------------------------------------------------------------------------------------------------------------------------------------------------------------------------------------------------------------------------------------|--------------------------------------------------------------------------------------------------------------------------|
| 
To determine the effect of adding an aldosterone receptor antagonism in patients on 1-5 below:
 
1. The individual components of the composite primary outcome
 | 
 
Hospitalisation or new onset heart disease (coronary heart disease, arrhythmia, atrial fibrillation, sudden death, resuscitated sudden death), stroke, transient ischaemic attack, peripheral arterial disease or heart failure.
 
 | 
 
Total occurrences
 
                                                      |
| 2. Measures of cardiovascular haemodynamics                                                                                                                                | 
 
Change in blood pressure annually and at final visit.
 
                                                                                                                                                                            | 
 
Annually and at final visit
 
                                            |
| 3. Measures of renal function                                                                                                                                              | 
 
Changes in NP
 
Change in ACR
 
Changes in eGFR
 
                                                                                                                                                                    | 
 
Change from baseline, annually and to final visit for NP, ACR and eGFR
 
 |
| 4. Healthcare cost evaluation                                                                                                                                              | 
 
Change in health status on EQ-5D-5L, KDQoL, (ICECAP-A and QoL VAS – Oxford only) and NHS resource use (records).
 
                                                                                                                 | 
 
Change from baseline, annually and to final visit
 
                      |
| 5. Safety                                                                                                                                                                  | 
 
Rates of hypotension (<100mmHg systolic or >20 mmHg systolic drop on standing)
 
Rates of adverse events
 
Rates of hyperkalaemia
 
                                                                            | 
 
Total occurrences
 
Total occurrences
 
                           |

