### 2.2.1 PRIMARY OUTCOME

Time from randomisation until the first occurring of death or hospitalisation for heart disease (coronary heart disease, arrhythmia, atrial fibrillation, sudden death, resuscitated sudden death), stroke, transient ischaemic attack, peripheral arterial disease or heart failure or first onset of any condition listed above not present at baseline. Primary endpoints will be adjudicated by an independent endpoints committee blinded to treatment arm.

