### 2.2.2 PRIMARY LONG-TERM OUTCOMES

Annual rates collected via medical notes review of death, hospitalisation for heart disease (coronary heart disease, arrhythmia, atrial fibrillation, sudden death, resuscitated sudden death), stroke, transient ischaemic attack, peripheral arterial disease or heart failure. First onset of any condition listed above not present at baseline.

The following variables will be used to record the occurrence of an event HOSPYN (hospitalised), FSONSETCVD (first onset of cardiovascular disease) and DEATHYN (death). In addition the endpoint will be adjudicated by the endpoint committee (DECISION). If the event is not judged to be an endpoint according to the protocol OR it is not the first onset of hospitalisation for CVD, or death OR there is insufficient information to determine it is an endpoint according to the protocol OR the endpoint committee determines it does not constitute as an endpoint for any other reason then the external adjudication will be coded "No". The reason that the event does not meet the endpoint condition will be captured in the variables REASONIFNO and OTHREASONIFNO. If any of the previously mentioned variables are coded "Yes" and DECISION is coded "Yes" then a primary outcome event will be recorded as having occurred.

If more than one primary outcome event has occurred, time to event will be computed using the date of the earliest occurring event minus RANDDAT (date of randomisation).

If a participant does not experience a primary outcome event they will be censored either at the date of last follow-up, the date of last contact or at the date of withdrawal from the study. Based on the intention to treat (ITT) principle, participants who withdraw from treatment but consent to further follow-up will be censored at the date of last contact rather than the date of withdrawal from treatment.

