#### 4.1.1 DEFINITION OF THE PRIMARY OUTCOME

If an event (as defined in section 2.2.1) occurs the primary outcome will be defined as time from randomisation (RANDDAT) to time of any of the following: time of first onset of or hospitalisation (HOSPDAT), time of first onset of cardiovascular disease (CVDSTDAT), or time of death (DEATHDATE). If multiple events occur then the primary outcome will be defined using the earliest occurring event. In addition, the adjudication by the endpoint committee will be used to determine if the event constitutes an endpoint as defined in the protocol (DECISION).

For those participants not experiencing a relevant event by the end of the study the primary outcome will be calculated as time from randomisation (RANDDAT) to censoring: either date of withdrawal if the participant has withdrawn completely from the study and further follow-up (LVISDAT) or date of last follow-up (VISDAT) if continuing follow-up. For participants who are withdrawn from treatment but consent to further follow-up, censoring will be based on date of last follow-up rather than date of withdrawal based on the ITT principle. Some participants may have multiple withdrawal dates, for example if a participant was withdrawn from medication for safety reasons but consented to further follow-up and then withdrew consent for follow-up at a later date. In these cases the date of final follow-up should be used as the date of censoring. A binary variable will code whether an event as defined in section 2.2.1 has occurred or the participant has been censored.

Two variables will be derived, PEVENT = 1, if the participant experiences a primary outcome event and 0 otherwise, DATEPEVENT = first occurring date of primary outcome event. Derived from:

PEVENT=1 if {{HOSPYN=Yes OR FSONSETCVDYN=Yes OR DEATHYN=Yes} AND {DECISION=Yes}}

PEVENT=0 if {HOSPYN=No AND FSONSETCVD=No AND DEATHYN=No} OR {ANY OF HOSPYN, FSONSETCVD, DEATHYN =Missing AND ALL NON MISSING HOSPYN, FSONSETCVD, DEATHYN =No} OR { ANY OF HOSPYN, FSONSETCVD, DEATHYN =Yes AND DECISION=No AND ALL NON MISSING HOSPYN, FSONSETCVD, DEATHYN =No}

IF PEVENT=1 THEN DATEPEVENT=Date first occurrence of ANY of HOSPYN, FSONSETCVD, DEATHYN, HDYN, STROKEYN, PADYN, HFYN

IF PEVENT=0 THEN DATEPEVENT={Date of last follow up OR date of last contact OR date of withdrawal IF FOLLOWUP=2}

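### The SAP's rules for coding a primary event conflict with its own definition of the third component, first onset of a listed condition without admission

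*Combined protocol and SAP*

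**What the plan says.** The definition is stated the same way in SAP 1.4, SAP 2.2.1 and protocol section 6. After death and hospitalisation for a listed condition, the third component is "First onset of any condition listed above not present at baseline". The test is per condition, against that participant's own history, and admission is not required.

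The rules that produce the event are in two other places.

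- SAP 2.2.2 names three event variables: HOSPYN for hospitalisation, and "FSONSETCVD (first onset of cardiovascular disease) and DEATHYN (death"). It then lists grounds for refusal by the endpoint committee, joined by OR. One of them reads "OR it is not the first onset of hospitalisation for CVD, or death OR there is insufficient information". If any ground applies, "then the external adjudication will be coded" No. The refusal reason is stored in REASONIFNO.
- SAP 4.1.1 sets PEVENT to 1 only when at least one of HOSPYN, FSONSETCVD or DEATHYN is Yes and DECISION is also Yes. The dates it names, besides that of hospitalisation, are "time of first onset of cardiovascular disease (CVDSTDAT), or time of death (DEATHDATE").

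SAP 4.1.1 also refers twice to events as 2.2.1 defines them, and describes DECISION as applying the protocol's definition.

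**The concern.** A single primary test needs a single rule for what counts. Here the definition counts a new outpatient diagnosis of, say, atrial fibrillation, transient ischaemic attack or peripheral arterial disease in anyone who did not already have it. The coding text can be read to count fewer of these, or none.

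The participants for whom this matters are in the trial. SAP 2.3.2 excludes clinical heart failure or known LVSD with a low ejection fraction, and recent myocardial infarction, but not other cardiovascular disease. SAP 3.2 records baseline ischaemic heart disease, atrial fibrillation, cerebrovascular and peripheral vascular disease, and SAP 7 plans a subgroup by baseline coronary artery disease. If the flag means first-ever cardiovascular disease, participants with coronary disease could reach the endpoint only by admission or death, while the others could also reach it by outpatient onset. The subgroup comparison would then set two different endpoints side by side.

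**Working it through.** The point rests on no stated figure, so the check sets the rules against one another.

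**Step 1. The refusal clause.** The grounds in SAP 2.2.2 are joined by OR, so one is enough. The first ground already covers events that are not protocol endpoints, so the hospitalisation clause is an additional ground. A new condition diagnosed without admission is neither a first cardiovascular hospitalisation nor a death. By the letter of the clause it is refused.

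**Step 2. Trace of a new listed condition without admission** (HOSPYN=No, DEATHYN=No):

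| Reading | No cardiovascular disease at baseline | Other cardiovascular disease at baseline |
|---|---|---|
| A. Refusal clause taken literally | DECISION=No, so PEVENT is not 1 | DECISION=No, so PEVENT is not 1 |
| B. Committee applies the protocol definition; flag means first-ever cardiovascular disease | FSONSETCVD=Yes, DECISION=Yes, PEVENT=1 | FSONSETCVD=No, all three flags No, PEVENT=0 |
| C. Clause and flag both read condition by condition, as in 2.2.1 | PEVENT=1 | PEVENT=1 |

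Only C matches the definition. It requires the refusal clause to be read against its wording and the flag description to be read more broadly than it is written. In the right-hand cell of B, a correct committee decision does not help, because DECISION=Yes cannot make PEVENT equal 1 while all three flags are No.

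**Step 3. Coding of refused events.** The prose of 4.1.1 makes PEVENT 0 whenever it is not 1. The coded rule differs. Its third PEVENT=0 clause requires some flag to be Yes while every non-missing flag is No, which cannot happen. With all three flags recorded there are 2 × 2 × 2 − 1 = 7 patterns with at least one Yes. With DECISION=No, all 7 satisfy neither PEVENT=1 nor any PEVENT=0 clause. DATEPEVENT is conditional on PEVENT, so these cases also get no date from the code.

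**Step 4. Planned event rate.** The cardiovascular rate in SAP 2.4 and protocol 12.3 counts hospitalisations only: 11.29 + 4.76 (total mortality) = 16.05 per 100 person-years for eGFR 30-44. Then 16.05 × 0.667 = 10.7 for eGFR 45-50, and (16.05 + 10.7)/2 = 13.4 overall, as stated. Onsets without admission are not in this rate, so leaving them out removes nothing that the sample size relied on.

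**Step 5. Number affected.** This would need the share of first events that are onsets without admission, and the share of participants with cardiovascular disease at baseline. The documents give neither.

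**The case against.** The strongest reply is that the intention is clear. SAP 4.1.1, the section that defines the primary outcome, points to 2.2.1 and to the protocol. Reading A leaves the onset flag with nothing to do, since every onset without admission would be refused. Sections 4.1.1 and 5.1 use a phrase that joins onset and hospitalisation with the word or, so the clause in 2.2.2 has probably lost that word. It also sits under the long-term outcomes heading. All of this stands, except that the heading settles little: the same text ends by recording a primary outcome event and uses the variables of 4.1.1.

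On the flag, the reply is that a short label on a form variable does not make it once per participant. DATEPEVENT draws on HDYN, STROKEYN, PADYN and HFYN, and the sponsor's transparency statement (protocol Appendix E) says peripheral arterial disease was listed individually on the endpoint form. This too is fair. A reader might infer that outpatient onsets were lost in everyone with prior cardiovascular disease. The documents do not support that, because the endpoint form and any adjudication charter are not among them. But the condition-level fields enter only the date rule, not PEVENT, so they do not remove the conflict.

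**Conclusion.** The conflict is real and concerns the primary outcome. Followed to the letter, the coding rules do not reproduce the stated endpoint, and no passage says which text governs. Repairing the probable slip in 2.2.2 resolves reading A but not reading B.

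The scope is limited to new listed conditions diagnosed without admission. Deaths and first cardiovascular admissions count under every reading.

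Two further inferences are tempting and should not be drawn. One is that true events were analysed as event-free time and the hazard ratio belongs to another endpoint; nothing in the documents shows that even one event was refused or missed under the literal wording. The other is a loss of power against the design; the planned rate counts cardiovascular admission plus death, so these onsets were never in the planned event count. The size of any effect cannot be computed from the documents.

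**What to change.** 1. In SAP 2.2.2, replace the clause so that, on this ground, an event is refused only if it is none of: (a) a death; (b) a hospitalisation after randomisation for a listed condition; (c) a first diagnosis after randomisation of a listed condition that this participant did not have at baseline, whatever other cardiovascular disease was present.
2. Define FSONSETCVD and CVDSTDAT by (c) in both 2.2.2 and 4.1.1.
3. Correct the third PEVENT=0 clause so that a refused event with no other accepted event is coded 0, as the prose of 4.1.1 already says.
4. Before lock, and blinded to arm, check two sets of reports against (a) to (c): events whose REASONIFNO says they were not a first onset, and reported new conditions with FSONSETCVD=No. The second set matters because those reports may carry no refusal reason.

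The cost is a wording and derivation edit, plus a small amount of blinded re-checking of data already held. Baseline history by condition is recorded (SAP 3.2), so no new patients or data collection are needed.
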